#### The modified OEP intervention

We will implement a culturally modified protocol still aligned with the US translated OEP model [29]. The 6-month protocol involves 3 home visits during the first 4 weeks, then 2 visits during the second month, followed by monthly visits during months 3 to 6. The final visit will take place during the 12th month to perform the final assessment. The monthly visits will serve as a motivator as well as ensure safe performance of the home exercise program. Former OEP trials have determined that the monthly visits or phone calls improve compliance and motivation. Many Zuni elders do not have phones. We have enhanced the communication by assisting participants to obtain a federally funded Lifeline cell phone available to rural residents. This has been used successful in a previous trial by the [name]. The same home visit schedule will be applied to the education control group.

#### The OEP intervention first visit

The first visit is a 60–75-min session to provide individualized exercise instruction (flexibility, balance, and lower extremity strengthening), review and set a schedule for exercises and the walking program. Participants will be advised and provided written instructions to perform balance exercises a minimum of three times per week, strengthening exercises three times per week, and a walking program up to 30 min three times per week. We will use a comprehensive walking plan of the OEP program. They will be provided with a 12-month calendar to keep track of their exercises and falls reporting. This will be checked monthly by the CHRs. In brief, as part of our continuous training and in-service, CHRs will ask about typical walking activity and undergo training to identify individuals with unsafe walking patterns (very slow walking, unsteady walking, etc.). The CHRs will encourage participants to break up the 30-min walking sessions into 10-min increments. As participant’s confidence increases, the walking program can include outdoor walking if it is safe to do so. Participants who can walk independently (per inclusion criteria) are typically safe to walk in their homes. All walking programs will start in the home and give participants the option to extend their program outside of the home. Two transportation vehicles have been purchased by Zuni Pueblo as part of this trial. The Zuni Health Initiative Clinic will provide transportation for walking indoors if weather conditions do not permit outdoor walking.

#### Subsequent OEP visits

Subsequent visits will be 30–60 min and provide a review of exercises and ongoing instruction in safe performance and progression. This program will be individualized by the CHR with physical therapist consultation to ensure the safe progression of upper extremity support for balance and use of leg weights for leg strengthening exercises. The home exercise program will be modified to ensure plain language text at an appropriate literacy level and include an option for large print to accommodate vision difficulties. The CHRs will ensure completion of the Falls Diary and exercise calendars, which is included in the OEP implementation manual. Finally, CHRs will perform assessments as described during the third month, at the end of the intervention (6 months) and at the conclusion of the protocol (12 months) [24]. The intervention will be a 6-month intervention and 6-month follow up (total 12 months), which aligns with US translation of OEP (CDC Compendium), and contribute to the sustainability of the program, minimize dropouts and facilitate sufficient time for data analysis for all enrolled participants [18, 30].

#### Education control arm

One hundred participants will be randomized into an education control arm. As part of the screening, they will have completed the *Stay Independent* self-assessment for falls risk. Within two months of the screening, CHRs will visit the education control participants’ homes and implement the education intervention. The education control protocol involves review of the: *Stay Independent, What You Can Do to Prevent Falls, Check for Safety,* and *Postural Hypotension: What It Is and How to Manage It* documents. These resources will provide structure to CHR-delivered education. Also, the control group will be provided information on available community resources (i.e. Zuni Senior Centre) and encouraged to implement home safety modifications. We estimate that CHRs will spend 10 min per document as part of the education control intervention. Participants will be provided written instructions and encouraged to maintain a falls and exercise calendar. The control group will receive monthly follow up visits to encourage compliance with the falls and exercise calendar, and undergo 3 reassessment visits at 3, 6, and 12 months. If an elder report a health concern, transportation and referral to Indian Health Service will be provided.

Aim 4 is to compare the effectiveness of the adapted OEP to an education-based fall risk management program in improving overall health status, self-management of daily activities, and social engagement. To achieve this, we will administer the Medical Outcomes Study Short Form 12 SF-12 Health Survey and Short Form PROMIS measures Self-Efficacy for Managing Daily Activities, and Ability to Participate in Social Roles and Activities to all randomized participants in both groups, at baseline, 6 and 12 months.

The Medical Outcomes Study Short Form 12 (SF-12v2) measures an individual’s perspective on health-related quality of life [25]. It addresses 8 domains; physical functioning, role; physical, bodily pain, general health perceptions, vitality, social functioning, role-emotional, and mental health. However, due to the limited number of items, composite scores represent physical health and mental health. We have validated the SF-12v2 instrument in Zuni adults [31]. Prior research has shown that higher SF-12v2 scores are associated with healthier behaviours, improved quality of life, and reduction in emergency department visits [32]. In addition to the SF-12v2 instrument, two measures from the Patient-Reported Outcomes Measurement Information System (PROMIS) will be utilized. The PROMIS Item Bank v1.0—Self-Efficacy for Managing Daily Activities – Short Form 4a demonstrates one’s confidence in performing activities of daily living and instrumental activities of daily living; essential for aging in place and preserving independence [33]. The PROMIS Item Bank v2.0—Ability to Participate in Social Roles and Activities- Short Form 4a measures one’s perceptions of ability to engage in leisure activities, family and work activities, and social engagement [26]. Both instruments are 4-question surveys and will take less than 10 min to administer. Finally, CHRs will administer the Attitudes to Falls-Related Interventions Scale (AFRIS) to measure attitudes to the fall risk management intervention [34–36]. It identifies positive, negative, and neutral attitudes as well as change over time. List of study related measures collected at baseline, 6 months, and 12-month assessment is presented in Table 1.

**Table 1 Tab1:** Schedule of testing

	Baseline	3 m	6 m	12 m
**Specific Aim 3 Measures**				
Brief Medical History & Comprehensive Falls Risk Screening	x			
STEADI Fall Risk Self-Assessment, Stay Independent	x			
STEADI Strength and Balance Tests (TUG, 30 Second Chair Stand, Four Stage Balance Test)	x	x	x	X
Monthly Falls Diary, Exercise Calendar and home visits	x	x	x	X
**Specific Aim 4 Measures**				
Attitudes to Falls-Related Interventions Scale (AFRIS)	x			X
Medical Outcomes Study Short Form 12 (SF-12v2)	x		x	X
PROMIS Self-Efficacy for Managing Daily Activities	x		x	X
PROMIS Ability to Participate in Social Roles and Activities	x		x	X
**Clinical Characteristics**				
Anthropological Measurement (Ht & Wt)	x			X
Orthostatic Blood Pressure	x	x	x	X

Changes in strength and balance (TUG, 30 Second Chair Stand, and Four Stage Balance test) are the primary outcome measures for this study. The CHRs will perform these assessments at baseline, 3, 6, and 12 months. Falls incidence is a secondary outcome and compared between the intervention and education groups. Fall incidence will be monitored prospectively monthly by falls calendars. We note that the high level of clinical surveillance of Zuni elders by the Zuni Senior Centre makes them an ideal population to record fall incidence and minimizes recall bias. Participants will be asked to maintain a monthly fall calendar throughout the investigation. A fall will be defined as an unexpected event where an individual unintentionally comes to the ground or lower level [37]. The CHRs will ask participants if they have fallen at every home visit. If a fall is reported, details of the fall(s), timing of fall, information about injury, and other pertinent information will be attained through standardized questionnaire. If an acute injurious fall is reported, CHRs will utilize a protocol (to be developed) for referral to IHS for follow up care and evaluation for ongoing participation in the trial. The fall diary will allow for the determination of number of falls, number of injurious falls and fall rate per person year. Fall diaries are the gold standard in fall assessment [38]. Collecting information on timing of fall will also allow for the examination of impact of the intervention on fall incidence.

The analysis plan for Aim 3, the randomized controlled trial, will employ an intention-to-treat analysis. We will first compare baseline demographic and clinical characteristics, such as age, sex, and fall risk score, between study groups using chi-square tests for categorical data and t-tests for continuous data. This will enable us to evaluate the degree to which the randomization scheme balanced these characteristics between the study groups, stratified by falls risk. As we expect randomization to provide for equivalent study groups at baseline, we do not expect to need to adjust for baseline characteristics in our primary analyses. However, we will change these plans should there be major differences in participant characteristics between treatment arms.

Falls incidence is not the primary outcome measure for this trial. Changes in balance and strength, as measured by the TUG, 30 Second Chair Stand, and Four Stage Balance tests will serve as primary outcome measures, which are important correlates of falls risk. We will employ linear mixed effects models to evaluate the significance of the treatment effect by testing for an interaction between treatment arm and time for these longitudinally measured assessments of the outcome measures. These models enable the efficient use of all measured data values while appropriately accounting for repeated measurements, and also the clustering that will be induced by stratified randomization of participants within household family units into strata defined by falls risk. Falls incidence is a secondary outcome. We will estimate and compare the incidence of falls observed within the two study groups over the study’s observation time using a score test from a Cox regression model that accounts for the clusters of individuals within household family units who were assigned to treatment groups within falls risk strata. In the absence of clustering, this is equivalent to a log rank test for time-to-event outcomes. This approach utilizes data from study participants, nested within household family units, while accounting for their time on study: those enrolled earlier in the study will have greater time in follow-up. We will also use Cox proportional hazards models to perform regression analyses that compare treatment groups while adjusting for potential differences in baseline characteristics.

In summary, first, we will follow the intent-to-treat principle in our primary analyses. Second, we will additionally adjust for the potential bias created by contamination using a contamination adjusted intention-to-treat analysis through the use of an instrumental variables (IVs) approach [39]. Third, we will carefully evaluate modelling assumptions (e.g. normality and variance structures in the mixed models, and proportionality of hazards in the survival models) in order to extract appropriate conclusions from the data. We will take corrective action when necessary, such as applying data transformations, to ensure that statistical modelling assumptions are met by the data. Finally, we will evaluate the degree to which missing data might have on study conclusions by performing sensitivity analyses that implement different rules from those induced by the intent-to-treat principle. Should these analyses suggest that the results differ by data missingness, we will explore the use of multiple imputation approaches and pattern mixture modelling approaches to determine the degree to which results differ under various missing data assumptions before making a final conclusion from the between-group comparisons.

In addition to these primary analyses, we will conduct a series of additional analyses to determine the degree to which the comparisons of interest might be influenced by patient characteristics. In particular, we are interested in whether the study comparisons are confounded, or modified by falls risk or complications of diabetes such as orthostatic hypertension/dizziness. We will perform analyses that examine the degree of confounding of the intervention effects by including them as covariates in the primary analysis models, and examine the degree to which they might modify intervention effects by adding their interactions with treatment arm to the primary analysis models.

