#### Randomization

After the initial screening eligible and willing participants will be consented (n = 200). At that time, they will be randomly assigned to either OEP or the control education arm, stratifying within levels of fall risk (low, medium, or high) and employing cluster randomization by household family unit. Random assignment will be made according to a random allocation list that will be generated upon study initiation. This list will be generated such that sequentially consented participants will be assigned to study arms according to the falls risk of the first enrolled family member. Our intent is to obtain roughly equal numbers of participants within each of the strata defined by falls risk. To avoid contamination, we will apply a single intervention to the members of a particular household family unit. Therefore, it is possible that the number participants within a treatment group may not be perfectly balanced across falls risk strata. This will have minimal impact on the outcome of the trial, particularly relative to the contamination problems that it overcomes. Treatment groups will be assigned randomly to household family units grouped within blocks. Blocks will comprise 2 or 4 household family units, and the sequence of block sizes will be randomly generated. This dual random allocation will ensure that the study arms will remain relatively balanced while enhancing masking of treatment allocation to those enrolling study participants. The screenings will be conducted at the Zuni Health Initiative Site. We can also arrange for screening at the elder’s home if that is their preference.

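### An undefined baseline-imbalance trigger decides covariate adjustment in the primary analysis, and the roles of the baseline outcome and the falls-risk stratum are not fixed

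*Protocol article*

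**What the plan says.** All of this is in the protocol article.

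- **Baseline comparison and trigger (Data analysis plans, Aim 3).** Characteristics such as age, sex and fall risk score are compared "between study groups using chi-square tests for categorical data and t-tests for continuous data". The authors state that "we do not expect to need to adjust for baseline characteristics in our primary analyses", and then that "we will change these plans should there be major differences in participant characteristics between treatment arms". No threshold, list of candidate covariates or form of adjustment is given.
- **Primary test (same section).** A linear mixed model is used for each of the three strength and balance tests, "testing for an interaction between treatment arm and time for these longitudinally measured assessments of the outcome measures". On timing: "The CHRs will perform these assessments at baseline, 3, 6, and 12 months". Baseline is therefore one of four repeated responses.
- **Falls-risk stratum.** Randomization describes "stratifying within levels of fall risk (low, medium, or high) and employing cluster randomization by household family unit", with the level taken from the first enrolled member of the household. The primary model is said to account for "the clustering that will be induced by stratified randomization of participants within household family units into strata defined by falls risk". The later paragraph on additional analyses names falls risk among possible confounders and effect modifiers, and plans to "examine the degree of confounding of the intervention effects by including them as covariates in the primary analysis models".

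**The concern.** Two things stand out.

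First, the covariates of the primary model depend on baseline data compared by arm. Under valid randomisation those comparisons can only detect chance. They do not show whether a covariate predicts the outcome, which is what makes adjustment worthwhile. A rule without a threshold also leaves the primary model open after the baseline data have been seen.

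Second, an arm-by-time test with unrestricted baseline means in each arm carries the full noise of the baseline measurement into the treatment contrast. When the within-subject correlation is low, as this plan assumes, that costs a lot of precision. The authors say that the Zuni elder population limits what can be powered, so avoidable loss matters more here than in a trial that can simply recruit more.

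**Working it through.** **Inputs.** From Power and sample size: within-subject correlation r = 0.3, within-cluster correlation 0.1, effect size 0.67, 80% power, two-sided 0.05 corrected for 3 tests, 84 per arm. From Table 1: visits at 0, 3, 6 and 12 months. Assumed here: Bonferroni correction (0.05/3), unit variance at each visit, equal correlation between visits, complete data, and clustering that inflates both analyses alike. The mean number of participants per household, m, is not stated.

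**The plan's own figure.** With change-from-baseline variance, n per arm = 2(z₁ + z₂)² × 2(1 − r) × [1 + 0.1(m − 1)] / 0.67². Here (2.394 + 0.842)² = 10.47, so n = 2 × 10.47 × 1.40 / 0.4489 = 65.3 before clustering. Rounded up, this gives 66, 72, 79 and 85 for m = 1, 2, 3 and 4. With baseline-adjusted variance (1 − r²) the results are 43, 47, 51 and 56. The stated 84 is approached only by the change-score form at about four participants per household. That hints at how the trial was sized but does not confirm it.

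**Single-visit contrast.** The variance factor is 2(1 − r) for change from baseline and 1 − r² with baseline adjustment.

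**Linear arm-by-time slope.** With free baseline means, the variance of the slope difference for one person per arm is 2(1 − r)/78.75, where 78.75 is the sum of squared deviations of 0, 3, 6, 12 from their mean 5.25. With a common baseline mean it is 2(1 − r) / [189 − 441r/(1 + 3r)], where 189 is the sum of squared times and 441 = 21² is their squared sum. At r = 0.3 these are 1.4/78.75 = 0.01778 and 1.4/119.37 = 0.01173, a ratio of 0.66.

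| r | 2(1 − r) | 1 − r² | Ratio | Variance cut, single visit | Variance cut, linear slope |
|---|---|---|---|---|---|
| 0.3 | 1.40 | 0.91 | 0.65 | 35% | 34% |
| 0.5 | 1.00 | 0.75 | 0.75 | 25% | 22% |
| 0.7 | 0.60 | 0.51 | 0.85 | 15% | 12% |

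At r = 0.3 the single-visit gain is worth 1/0.65 = 1.54 times the participants; at 0.7 it is 1/0.85 = 1.18 times. The comparator matters: against a follow-up-only comparison, adjustment at r = 0.3 saves only r² = 9%.

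**The trigger.** The article gives neither the number of baseline tests nor a level. If there were 3, 5 or 10 independent tests at 0.05, the chance of at least one significant result under valid randomisation would be 1 − 0.95³ = 14%, 1 − 0.95⁵ = 23% or 1 − 0.95¹⁰ = 40%.

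**The stratum.** Set side by side, the primary-model paragraph mentions falls-risk strata only as part of clustering, and the additional-analyses paragraph adds falls risk as a covariate. If the same variable were already a fixed effect in the primary model, that second step would be redundant. The two could also be different variables, because the household's stratum comes from its first enrolled member and need not match each person's own risk.

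**The case against.** The strongest reply is that the primary test is a valid intention-to-treat analysis and that the precision argument rests on a detail the article does not state. An arm-by-time test can be run with free or with common baseline means, and a condensed article may leave that choice to the analysis plan. This stands, so the precision loss is conditional on free means. The trigger is different: it is a stated rule, not a silence.

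A second reply is that under free baseline means the trigger hardly touches the primary test. A covariate or stratum added only as a main effect cancels from the arm-by-time contrast. With 80 per arm, complete data and r = 0.3, the 12-month contrast has variance 2 × 1.40/80 = 0.035 with or without the stratum; under about 20% assumed dropout it was 0.0399 either way. This also stands, although the article does not limit the change of plan to main effects.

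A reader might infer more than the text supports:

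- **That the baseline outcome is left out.** It is a response in the model. What is not stated is a common mean or conditioning on it.
- **That the stratified design is ignored.** The article says the model accounts for it; the form is unclear.
- **That the detectable effect at 80 per arm would fall from 0.69 to 0.55.** This scales 84 per arm by 0.67 × √(84/80) = 0.69, then 0.69 × √0.65 ≈ 0.55. It presumes a change-score basis that the article does not confirm, and the article's own figure with 20% dropout is 0.59.
- **That unblinded staff choose the model.** Strengths and limitations says outcome assessment is not blinded. It does not say who makes the baseline comparison.

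**Conclusion.** The point holds in a limited form. The plan makes baseline adjustment of the primary analysis depend on an undefined difference between arms, which after randomisation is chance. It also does not settle how the baseline outcome and the falls-risk stratum enter the model.

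If baseline means are free by arm, fixing the baseline handling cuts the variance of the treatment contrast by 34-35% at the plan's own correlation of 0.3, by 22-25% at 0.5 and by 12-15% at 0.7. These figures assume complete data, equal correlation between visits and the same clustering inflation for both analyses. They come from the baseline outcome alone; the article gives nothing from which to size the stratum's contribution. Nothing here shows bias in the planned test.

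**What to change.** - **Delete the trigger.** Baseline characteristics can be tabulated by arm, but should not decide the model.
- **Fix the primary model now.** For each primary outcome: a linear mixed model with categorical visit, arm-by-visit effects at 3, 6 and 12 months, a common baseline mean (or the baseline value of that outcome as covariate), the household's falls-risk stratum as used at randomisation as a fixed effect, and a household random effect alongside the repeated-measures structure.
- **Reconcile the two statements on falls risk.** Say that the randomisation stratum belongs to the primary model, and name any individual-level falls-risk variable kept for additional analyses.
- **Aim 4.** Use the same form at the visits in Table 1: 6 and 12 months for SF-12v2 and the two PROMIS measures, and 12 months only for AFRIS. The 3-month term does not carry over. The training text under Aim 2 lists 3, 6 and 12 months for these measures, so confirm the schedule at the same time.

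The cost is analysis-plan wording. The variables are already collected, and no visit or sample-size change is needed. The change should be dated before any comparison by arm is made.

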## Background

A growing source of health disparities is the epidemic of falls and associated injuries in socio-economically disadvantaged and geographically isolated American Indian communities. Falls are particularly serious for older American Indians who experience more comorbidity and chronic illnesses than the general population [1]. The unintentional fall death rate is higher in American Indians from the Southwestern US than other regions of the US and is higher in New Mexico (NM) than other regions of the US [2]. The latest available data in 2017, reported that unintentional fall-related injury was the leading cause of unintentional injury-related death, hospitalization and emergency department visits for older New Mexicans [3]. A Tribal Behavioral Risk Factor Surveillance Survey of NM tribes conducted by the Albuquerque Area Southwest Tribal Epidemiology Center reported that 32% of American Indian adults 65 + experienced at least one fall in the past three months. Among those who reported a fall, 30% sustained an injury [4]. Compounding these statistics, the fall-related mortality rates increased dramatically from age 50 years, which is 15 years younger than the national trend [5]. Fall-related injuries place older adults at risk of losing independence, and the New Mexico Department of Health reports that only 25% of adults hospitalized for a fall-related injury are discharged directly home [5]. The Zuni Pueblo in New Mexico is geographically isolated with limited access to rehabilitative services. If a Zuni elder sustains a fall-related injury, the closest tribal assisted living or skilled nursing facility is 100 miles from the reservation. Thus, fall risk and rates reduction is essential for this vulnerable community.

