### Participant characteristics

#### Inclusion

Zuni elders will be eligible to participate if they are Zuni tribal members aged 65 years and older who demonstrate elevated fall risk according to 2 or more of the following outcomes: (1) Timed Up and Go ≥ 12 s; (2) 30 Second Chair Stand Test below age and sex norms; (3) Inability to complete the Four Stage Berg Balance Test; (4) Four or more positive responses on the *CDC Stay Independent: Check Your Risk for Falling*; or (5) history of 2 or more falls during past year or one injurious fall during past year.

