#### Power and sample size

The primary outcomes of this study are changes in the TUG, 30 Second Chair Stand, and Four Stage Balance tests. These outcomes were selected because they are related to falls risk. Although the aim is to eventually demonstrate a reduction in falls incidence, the Zuni elder population is not big enough to provide adequate statistical power for this outcome. We do plan to extend the follow-up falls calendars to capture these outcomes, and this will provide critical information for future studies. The accepted degree of reduction in falls that is imparted by a traditional OEP is 32% [38, 39]. Because the percent reduction in falls does not directly correlate with a quantitative effect size that will be estimable from the data addressing our primary hypotheses, and because the outcome measures do not perfectly predict the probability of falls, it is likely that the detectable effect size that would be meaningful in the context of reducing falls would need to be a large one in order to suggest that the intervention is likely to have the desired effect on falls incidence. Therefore, the study was powered to detect at least moderate effect sizes. Specifically, we computed the number of participants to enrol into the study that would provide us with at least 80% power to detect an effect size of 0.67 for an improvement in the outcome measures over time between the treatment arms using a two-sided, 0.05 level test of between-group differences over time. Power estimates were obtained from linear mixed effects models that assumed within-subject correlations of 0.3, and within-cluster correlations of 0.1, and also corrected for 3 primary tests of significance. This computation suggested that data from 84 participants in each treatment arm would be required. In order to allow for the potential for dropouts, or for the possibility that the treatment might not be quite as efficacious as desired, 100 study participants per treatment arm will be enrolled. Even if 20% of the participants drop out of the study, this sample size will provide at least 80% power to detect effect sizes of 0.59 – nearly the target of 0.67, and still not a large effect size.

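### The between-arm test of falls, on its natural reading, uses one fall per person, although the diaries record every fall and a rate per person-year

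*Protocol article*

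**What the plan says.** All references are to the protocol article.

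- **Data collected** (Data analysis plans): "The fall diary will allow for the determination of number of falls, number of injurious falls and fall rate per person year". The timing of each fall is recorded as well.
- **Comparison** (Data analysis plans, Aim 3): "We will estimate and compare the incidence of falls observed within the two study groups over the study’s observation time", to be done "using a score test from a Cox regression model that accounts for the clusters of individuals within household family units". The next sentence fixes what kind of test this is: "In the absence of clustering, this is equivalent to a log rank test for time-to-event outcomes". Adjusted Cox models follow.
- **Correlation**: the only clustering named for falls is that of individuals within households. For the primary outcomes, the same paragraph says that the models account for repeated measurements. Nothing comparable is said about repeated falls in one person.
- **Power** (Power and sample size): the population is said to be too small for adequate power on falls. Extended falls calendars are planned to inform future studies.

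**The concern.** A log-rank test takes one event time per person. Read that way, a participant stops contributing after the first fall, and later falls in the diary play no part in the only between-arm test stated. The rate per person-year, which is the quantity closest to the aim of reducing falls, has no stated between-arm comparison.

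Repeat falls are likely to be common here. The Background reports that "32% of American Indian adults 65 + experienced at least one fall in the past three months", a figure for that age group in general. The trial selects people at elevated risk, and one entry criterion is a "history of 2 or more falls during past year or one injurious fall during past year".

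At stake is information on a secondary outcome that is already short of it. The planned calendar extension would also add little to a first-fall test. At the constant rate derived below, 1 − 0.786 = 21% of controls and about 35% of OEP participants would still be free of a fall at 12 months.

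**Working it through.** The article gives no event count or power figure for falls, so there is none to reproduce. The check asks how much a first-fall test leaves out, and what that costs in power.

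**Inputs from the article**
- 32% with at least one fall in three months (Background).
- A 32% reduction in falls with traditional OEP (Power and sample size), taken as a rate ratio of 0.68.
- 12 months of observation (Subsequent OEP visits).
- 100 per arm with 20% dropout (Power and sample size), so 100 × 0.8 = 80 per arm.

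**Assumptions not in the article**
- A constant fall rate over time.
- Gamma between-person variation (frailty) with variance k from 0 to 2.
- Two-sided 0.05 for falls; the article states this level for the primary outcomes.
- No household clustering.

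**Step 1: share of falls left out.** Choose the control mean m per year so that the chance of a fall in three months is 0.32.
- k = 0: m = 4 × (−ln 0.68) = 1.54.
- k > 0: m = 4 × (0.68^(−k) − 1)/k.

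The chance of at least one fall in 12 months is P(m) = 1 − exp(−m) for k = 0, and 1 − (1 + km)^(−1/k) otherwise. The OEP mean is 0.68m. The pooled share left out is 1 − [P(m) + P(0.68m)] / (1.68m).

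| k | m | P(m) control | First falls / all falls, 100 per arm | Share left out |
|---|---|---|---|---|
| 0 | 1.54 | 0.786 | 144 / 259 | 45% |
| 0.5 | 1.70 | 0.708 | 131 / 286 | 54% |
| 1 | 1.88 | 0.653 | 121 / 316 | 62% |
| 2 | 2.33 | 0.579 | 109 / 391 | 72% |

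Sensitivity to the three-month proportion, over k = 0 to 2: at 15% the share is 24% to 48%, and at 20% it is 30% to 57%.

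**Step 2: power.** This was simulated with 80 per arm over 12 months. The log-rank test on the first fall is set against a test of the log rate ratio on all falls with empirical variance. Each cell gives first fall / all falls.

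| When the rate ratio 0.68 applies | k = 0 | k = 0.5 | k = 1 |
|---|---|---|---|
| Months 0–12 | 56% / 80% | 36% / 61% | 27% / 46% |
| Only after month 3 | 21% / 53% | 14% / 37% | 10% / 29% |
| Only months 0–6 | 25% / 27% | 17% / 18% | 14% / 15% |

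For months 0–12, a normal approximation for the negative binomial rate ratio gives 78%, 60% and 47% at 80 per arm. This agrees with the all-falls column.

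**Step 3: proportional hazards.** With a constant rate ratio of 0.68 and gamma variation, the first-fall hazard ratio at t years is 0.68 × (1 + kmt)/(1 + 0.68kmt). At 12 months:
- k = 0.5: 0.68 × 1.851/1.579 = 0.80.
- k = 1: 0.68 × 2.882/2.280 = 0.86.

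So between-person variation pulls the first-fall hazard ratio towards 1 even when the effect on the rate is constant. A delayed effect would also make the hazards non-proportional.

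**The case against.** **The event is not defined.** The words "first fall" appear nowhere. A Cox model in counting-process form could use every fall, and a household-level robust variance would also cover correlation among one person's falls, since each person belongs to one household. This stands in part: one event per person is an inference. But without household clustering, an all-falls model would still have to handle dependence within a person, so the stated log-rank equivalence would not hold. If all falls were intended, that sentence needs correcting anyway.

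**Early first falls.** A reader might infer that proportional hazards fail because first falls concentrate in the early months. They do concentrate: at k = 0, 0.32/0.786 = 41% of control first falls come by month 3. But a constant hazard produces the same pattern, and it is compatible with exact proportionality. Only between-person variation or a change of effect over time breaks it.

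**Assumption checks.** The plan commits to checking proportionality and taking corrective action. That is to its credit, but such steps would not bring unused falls back into the comparison.

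**Timing of benefit.** The article gives no onset or duration of effect, and the intervention lasts 6 of the 12 months. If benefit ends with it, the power advantage disappears. This stands. In none of the effect patterns examined was the rate comparison materially worse.

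**Consequence.** Falls are secondary and conceded to be underpowered, the rate can be reported descriptively, and time to first fall is a legitimate quantity that limits the weight of very frequent fallers. This also stands, and it limits the severity.

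**Conclusion.** The point holds as a mismatch between the falls data collected and the between-arm test stated for them. On the natural reading, and if the Background's 32% carries over, the test leaves out about 45% of falls with no between-person variation and 54% to 62% with variance 0.5 to 1. The power cost is roughly 19 to 25 percentage points if the effect lasts 12 months (80 − 56 = 24, 61 − 36 = 25, 46 − 27 = 19). It is larger in relative terms if benefit starts after month 3, and nil if it ends at month 6.

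These sizes rest on an assumed dispersion, on a survey figure not drawn from trial participants, and on persistence of the effect. A reader might therefore infer two stronger claims that the article does not support. One is that at least half of the falls are certain to be discarded; with a three-month proportion of 15% the share would be 24% to 48%. The other is that the Cox test is invalid; under no effect, both methods rejected in about 5% to 6% of simulated trials. This is a worthwhile, cheap improvement to a secondary analysis.

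**What to change.** Make the between-arm falls comparison a negative binomial model of all falls per person, with log person-time as offset, falls-risk stratum as a fixed effect and household-robust standard errors, reported as a rate ratio with its confidence interval. Specify the same model for injurious falls. Keep the Cox analysis as supportive, and label it as time to first fall.

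The offset handles the unequal follow-up that the plan expects, and the model can use the extended calendars. The rate ratio also sits more directly beside the 32% reduction that the plan cites.

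The cost is analysis-plan wording; no data collection changes. One small downside is that very frequent fallers carry more weight. The robust standard errors and the supportive first-fall analysis cover this.
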